## Abstract

**Background:**

Major depression is one of the main mental illnesses in old age, with acute exacerbated episodes requiring treatment in geriatric psychiatry. A meta-analysis showed that aerobic exercise in moderate intensity has large effects in older adults with major depression, but there is no evidence of aerobic exercise in geriatric psychiatry. Therefore, this study aims to analyze the feasibility and effects of an ergometer-based aerobic exercise on depressive symptoms.

**Methods:**

A single-center randomized controlled trial will be conducted in an acute geriatric psychiatric hospital. Inpatients allocated to the intervention group will receive a 2-week aerobic ergometer program. The control group will receive seated flexibility exercise in addition to usual care. The overall effects on the patients’ depressive symptoms will be measured by clinical global impression of change (CGI) as the primary outcome. Changes in depressive symptom domains, physical (in)activity, and aerobic performance as well as the dosage of applied antidepressants will be examined as secondary outcomes.

**Discussion:**

This short-term aerobic exercise program is expected to decrease depressive symptoms in acute exacerbated periods in older adults. The results may increase the evidence for implementing physical activity interventions in acute hospital settings. The disease-related motivation for exercise in acute exacerbated depressive periods will be the most challenging aspect. The treatment of depression requires new cost-effective approaches, especially in acute geriatric psychiatry with potential benefits for patients, family members, and clinicians.

**Trial registration:**

German Clinical Trial Register ID: DRKS00026117

**Trial status:**

Protocol Version 1.2 dated February 23, 2022. By February 23, 2022, the trial had recruited a total of 15 participants in two wards at the Department of Geriatric Psychiatry at the LVR-Hospital Cologne. Recruitment started on November 12, 2021. The recruitment is expected to continue for at least 12 months.

## Background

Depression is a common disorder in old age [1] that affects around 7% of the older global population [2]. In Germany, 1.4 million adults above 65 years suffer from clinical depression, representing 8.1% of the population with 8100 cases per 100,000 residents [3]. The Global Burden of Disease (GBD) Study by the World Health Organization indicated that depression is one of the leading causes of disability [4]. The pathophysiology of depression has not yet been clarified, but the most common theory is the “monoaminergic hypothesis,” which identified a change in serotonin, dopamine, and/or norepinephrine metabolism [5, 6]. Neuroinflammation and chronic stress due to disruption of the brain-derived neurotrophic factor (BDNF) or transforming growth factor-β1 are also discussed in the context of the disease with negative effects on neuroplasticity [7].

Late life depression is associated with a higher risk of suicide [8] and decreased functioning [9], which comes with limitations in activities of daily living (ADL) [10] and leads to a deterioration in quality of life [11]. Besides the main affective symptoms like low mood, loss of interest, and fatigue [12], depression is a major predictor for cardiovascular and neurodegenerative diseases and increases mortality risk in older adults by 28% [13].

Acute exacerbated periods of the disease are treated in acute geriatric psychiatry, with an average hospital stay of 4 weeks and respective outpatient aftercare [14]. Antidepressant drug therapy is considered as first-line treatment with selective serotonin re-uptake inhibitors [15]. A recent review recommends physical activity as a complementary treatment approach to antidepressant drug therapy [16]. The authors concluded that older patients with late-life depression, who are at high risk of developing dementia, could benefit from this synergistic effect in particular. The biologically-based impact of physical activity on neuroplasticity, such as hippocampal neurogenesis, has already been explained [17]. Aerobic exercise has an impact on tryptophan hydroxylase, which is needed for the synthesis of serotonin [18] and increases BDNF levels [19–21], thus stimulating neuroplasticity and neurogenesis [16].

A short 10-day inpatient exercise treatment of major depressive episodes in middle-aged adults, aged 49 ± 13 [22] and 45.3 ± 10.6 [23] showed large effects favoring the aerobic intervention [22, 23] over stretching or no intervention. The aerobic exercise included brisk walks or jogging [23] or treadmill walking [22]. Meta-analyses showed that physical exercise is associated with significantly lower depression symptoms in older adults [24, 25]. Physical activity has the potential to positively influence mood in depressive disorders. There are several mechanisms of action for this, such as hormonal changes, effects on neurogenesis, inflammation, and oxidative stress, to changes in corticular activity and structure [25]. Studies included in the meta-analysis were conducted in an outpatient setting or in nursing homes with a minimum treatment period of 3 months. In particular, aerobic exercise and moderate intensity showed large effects in the treatment of depression [25]. A recent meta-analysis reported that aerobic exercise, such as walking or ergometer-based cycling, can be considered as safe and natural training for the older population [26].

To date, there is no evidence of short-term aerobic exercise in the treatment of old-age depression. Considering the positive effect on short-term inpatient treatment for a duration of 10 days in middle-age adults [22] and the lack of evidence in acute geriatric psychiatry, we aim to set up a randomized controlled trial (RCT) investigating the effect of aerobic exercise in older adults during acute exacerbated periods of major depression.

## Objectives

The primary objective of this trial is to analyze the feasibility and effects on depressive symptoms within a 2-week aerobic exercise program for inpatients in acute geriatric psychiatry.

We hypothesize that the intervention group (IG), carrying out a 2-week-aerobic exercise program in addition to treatment as usual (TAU), shows effects on depressive symptoms and physical activity at post-intervention as compared to the control group (CG).

## Methods

### Study design

A monocentric randomized controlled superiority trial with pre- and post-intervention assessment will be conducted with 1:1 allocation ratio in the department of Geriatric Psychiatry at the LVR-Hospital Cologne (Fig. 1). The Ethics Commission of North-Rhine Medical Chamber obtained ethical approval (reference number: AZ 2018192). This trial is registered in the German National Register of Clinical Trials DRKS00026117. The protocol is reported according to the Spirit guidelines.

**Fig. 1 Fig1:**
[figure not shown]
Study flow-chart

### Sample

Patients from two hospital wards will be screened for eligibility by a senior psychiatrist who is not involved in the study team. The inclusion and exclusion criteria are presented in Table 1. Written informed consent from the patient’s legal guardian or the patient was required. In accordance with the ethical approval and the task force on ethical and legal questions of the Association of Neuropsychopharmacology and Pharmacopsychiatry, the following consent for participation will be conducted [27]: With a score < 20 on the Mini-Mental Status Examination (MMSE) [27], the patient’s legal guardian was asked to give informed consent; for scores of ≥ 20 and the ability to explain the content and aims of the project in the patient’s own words, the patient was considered to be able to give the informed consent on its own.

**Table 1 Tab1:** Inclusion and exclusion criteria

Inclusion criteria	Exclusion criteria
Diagnosis of depression according to ICD-10 (F31.3–F34)	Clinical exclusion of delirium (based on CAM); combined diagnosis of depression and an alcohol-induced neurodegenerative disease
Minimum length of stay of 3 days before enrollment in the study	Acute and/or severe cardiac disorder, neurological disease, and/or chronic orthopedic disorder
MMSE ≥ 19 points and the ability to explain the content of the study in the patients’ own words^a^	MMSE < 19 points
Prescription for exercise therapy (this includes cardiovascular capacity)	

*ICD-10* International Statistical Classification of Diseases and Related Health Problems, *CAM* confusion assessment method [28], *MMSE* Mini-Mental Status Examination, maximum score of 30 points, higher score indicating better cognitive functioning

^a^This approach is consistent with the Society for Neuropsychopharmacology and Pharmacopsychiatry Working Group on Ethical and Legal Issues [27]

As part of routine care, baseline characteristics are recorded within the geriatric assessment, which is carried out by a nursing and medical staff member of the LVR-Hospital Cologne. The geriatric assessment includes sex, age, weight and height, clinical diagnosis, MMSE [29], and Timed Up and Go Test (TUG) [30].

### Sample size calculation

The required calculation of the sample size is performed by using G*Power 3.1 [31]. Based on the results of the current state of studies [24] a moderate effect size is assumed for the change in depressive symptoms. The effects of Bridle’s pooled analysis show an effect size of -0.44 SMD for studies with an active control group. This corresponds most closely to the present methodology with an active control group. The sample required to detect statistically significant differences in the depressive symptoms for a two-tailed test of the proportions with an effect size of d=0.5 was calculated for the primary objective. Based on this calculation, we will include 100 patients in the trial, with 50 allocated to each study group. The allocation rate is 1:1, two measurements, non-parametric analysis due to ordinal characteristics of the instruments and a-error of 0.05 and a power of 0.95 (1-ß-error) according to Cohen [32].

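### Fifty patients per arm do not give the stated 95% power: the protocol's own inputs give about 68–70% at d=0.5, and about 57–59% at the cited effect of 0.44

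*Protocol article*

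**What the plan says.** The section Sample size calculation (protocol article, Methods) gives all the inputs and the result:

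- **Test and effect:** "a two-tailed test of the proportions with an effect size of d=0.5".
- **Error rates:** "a-error of 0.05 and a power of 0.95".
- **Design:** "The allocation rate is 1:1, two measurements, non-parametric analysis due to ordinal characteristics of the instruments".
- **Evidence for the effect:** a pooled analysis is said to "show an effect size of -0.44 SMD for studies with an active control group", and of this figure the protocol says "This corresponds most closely to the present methodology with an active control group".
- **Result:** "Based on this calculation, we will include 100 patients in the trial, with 50 allocated to each study group".

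Elsewhere, Study design describes a two-arm superiority trial. Objectives states the hypothesis as intervention against control. Table 2 and Primary outcome define the primary endpoint as the CGI global improvement scale, a clinician's rating from 1 to 7. Analysis plans a one-way repeated-measures ANOVA or a Friedman test.

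**The concern.** The stated inputs can be checked directly, and 50 per arm looks too few by about half. The total of 100 is close to the number normally needed in each arm for d=0.5 at 95% power. Per-arm and total may have been confused, but the document cannot confirm this.

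The description of the test adds doubt. A test of proportions does not take d as its effect size, and neither fits an ordinal 7-point rating. The planning effect is also somewhat larger than the cited 0.44.

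The stated power governs how a non-significant result is read. A reader told that the trial had 95% power will take a null result as strong evidence against a moderate effect. If the real power is near two in three, that reading is not justified.

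**Working it through.** **Inputs**, all from Sample size calculation: two-sided alpha 0.05, target power 0.95, d=0.5, cited effect 0.44, 50 per arm, non-parametric analysis of two arms.

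**1. Does the stated calculation give 50 per arm?**

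Normal approximation, per arm: n = 2(z₀.₉₇₅ + z₀.₉₅)²/d², with (1.960 + 1.645)² ≈ 12.995.

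- d=0.5: 2 × 12.995/0.25 = 103.96, so 104.
- d=0.44: 2 × 12.995/0.1936 = 134.2, so 135.

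The non-central t gives 105 and 136. For the Wilcoxon-Mann-Whitney (WMW) test, dividing the t-test size by its asymptotic efficiency under normality, 3/π = 0.955, gives 110 and 142. The stated 50 is not reproduced.

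**2. What power do 50 per arm give?**

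The non-centrality is d√(n/2) = 0.5 × √25 = 2.5. Power is approximately Φ(2.5 − 1.96) = Φ(0.54) = 0.705. At 0.44 it is Φ(2.2 − 1.96) = Φ(0.24) = 0.595. For WMW, the effective n is 50 × 0.955 = 47.7.

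| | Normal | t | WMW |
|---|---|---|---|
| Power at d=0.5 | 0.705 | 0.697 | 0.6765 |
| Power at d=0.44 | 0.595 | 0.586 | 0.567 |
| n per arm for 95%, d=0.5 | 104 | 105 | 110 |
| n per arm for 95%, d=0.44 | 135 | 136 | 142 |
| d detectable at 95%, 50 per arm | 3.605/5 = 0.72 | 0.73 | 0.75 |

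A WMW simulation with 20,000 replicates gave 0.683 at d=0.5 and 0.563 at 0.44 on continuous normal data. With a latent normal cut into seven categories (assumed cut-points ±0.4, ±1.2, ±2) it gave 0.656 and 0.545, so ties cost a little more.

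**3. Does another reading give 50 per arm (100 in total) at 95%?**

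- *Proportions.* Reading 0.5 as Cohen's h gives 104 per arm, and 50 per arm gives 0.705.
- *One-sided.* This contradicts the text. It needs 88 (t) or 92 (WMW) per arm, and 50 per arm gives 0.799 or 0.782.
- *Paired test in one group.* At d=0.5 this needs 54 pairs (t) or 57 (signed-rank), and 50 pairs give 0.934 with the t-test. It tests pre-post change within one arm, not one arm against the other.
- *Repeated-measures ANOVA, main effect of group,* f=0.25, two measurements. N is 106 in total at correlation 0 and 158 at 0.5. This test averages the baseline into the outcome.
- *Repeated-measures ANOVA, group-by-time interaction,* f=0.25, non-centrality f²·N·2/(1 − ρ). N in total is 106 at ρ=0, 96 at ρ=0.1 and 54 at ρ=0.5. At ρ=0.06, N=100 gives 0.951. However, in a 2×2 interaction f=0.25 means a between-arm difference in change of 4 × 0.25 = 1.0 SD, twice the stated 0.5.
- *ANCOVA on an outcome with a baseline,* d/√(1 − ρ²). At d=0.5 and 50 per arm, power is 0.816 at ρ=0.5, 0.934 at 0.7 and 0.963 at 0.75. Reaching 95% needs ρ ≈ √(1 − (0.5/0.728)²) ≈ 0.73.

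**4. Which readings suit the primary endpoint?** The CGI global improvement scale is itself a rating of change. It has no baseline value of its own, so it has no pre-post correlation to exploit. The applicable comparison is between the two arms on one rating, as in steps 1 and 2.

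**The case against.** The strongest reply is that the 68–70% assumes a single-timepoint test that the protocol never names. Sample size calculation lists two measurements, Outcome measures gives pre- and post-intervention time points for the primary outcome, and Analysis plans repeated-measures methods. With a baseline, power depends on a correlation that is not stated, and a high enough value would bring ANCOVA to 95%. A repeated-measures interaction with a correlation near 0.06 gives almost exactly 100.

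This stands in part. The figure of 100 can be reached in software, so it should not be called unreachable, and the 68–70% does depend on reading the CGI scale as a single rating. That reading follows from Table 2 and Primary outcome. The alternatives need either a correlation of about 0.73 or a 1.0 SD difference in change, and the protocol states neither. The conflict with the pre/post and repeated-measures wording is real, and the correction has to resolve it.

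Three smaller points are also fair:

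- Planning on 0.5 with 0.44 shown beside it is an open choice, so the 0.44 results are a sensitivity check on the protocol's own evidence.
- An article may leave attrition to the full protocol. A 10% loss is purely an assumption here. It would leave 45 per arm and power of about 0.65 (t) or 0.63 (WMW) at d=0.5.
- The seven-category simulation depends on its assumed cut-points.

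None of these restores 95% power.

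**Conclusion.** The stated power is wrong as written and must be corrected. The planned size is less than half of what the stated inputs require. The risk of missing d=0.5 is 30–32% (1 − 0.697 and 1 − 0.6765), against the 5% implied, and 41–43% at 0.44.

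This rests on a two-sided between-arm comparison of one post-treatment CGI rating, full follow-up, and near-normal efficiency for the rank test. Ties or dropout would lower power somewhat further. A full protocol or analysis plan could add detail, but it could not make the inputs stated here give 95% power at 50 per arm for that comparison.

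**What to change.** Keep 100 patients and replace the power statement with wording such as:

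> With 50 patients per arm, a two-sided Wilcoxon-Mann-Whitney test at the 0.05 level has about 68% power for d=0.5 and about 57% for d=0.44. Power of 95% is reached only for d of about 0.75.

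Also:

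- Remove the references to a test of proportions and to two measurements from the calculation.
- Name the same between-group test for the primary outcome in Analysis, and align the primary-outcome time points in Outcome measures with a single post-treatment rating.
- If the sponsor instead intends a baseline-adjusted analysis of an outcome that has a baseline, state that outcome and the assumed correlation, and recalculate.
- Report the primary effect with its confidence interval, so that a null result is not over-read.

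The cost is a change of wording in these sections and in any registry entry that repeats the figure. No patients are added, but the declared power becomes less favourable. Only 15 patients had been recruited at the date of this protocol version, so at that point the correction could be made well before any analysis.

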### Allocation

With an informed consent and pre-assessment, randomization will be performed via stratified randomization. An organizational staff member, who is not part of the study team, will perform the group allocation. Study randomization was done through Study Randomizer (2017), a web-based randomization service [33]. In order to achieve the best possible balance between the two study groups, the factors, sex, age, and MMSE score [29] will be weighted 1:1 in the program. Patients are sequentially numbered, no conclusion can be drawn about the patients, with the exception of the study director who takes the patient's informed consent.

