### Primary outcome

The primary outcome of the intervention is the change in depressive symptoms rated by the clinical global impression of change (CGI). The CGI is performed by the clinician and includes a 1- to 7-point rating scale of the global improvement due entirely to treatment [34].

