### Secondary outcomes

As a secondary outcome, the symptom domains and the severity of depressive symptoms will be measured by self- and peer-rated assessments. The Beck Depression Inventory (BDI II) [35] is a self-rated scale which is conducted with the patient in interview form. The Hamilton Rating Scale for Depression (HAMD) [36] is performed by the nursing staff members. Mobility-related measurements, such as physical in(activity), will be performed with the Dynaport Move Monitor + (MM+; McRoberts, The Hague, NL). The MM+ consists of an accelerometer, a gyroscope, a magnetometer, a barometer and a temperature sensor. The raw data will be processed using the manufacturer’s own algorithms. The corresponding output includes the type of activity and body positions (walking, stair walking, cycling, shuffling, standing, sitting, and lying) and an additional category not-worn, corresponding MET-values, activity duration, and number of steps per 60-s epoch. Data will be collected for a 48-h period, starting and ending at 12 am on days one and three. The sensor is attached to the lower back approximately 3 cm to the right of the fifth vertebra of the lumbar spine (L5) with a waterproof self-adhesive foil (Opsite Flexifix, Smith and Nephew, London, UK) [39]. The participants will be asked not to remove the sensor during the measurement period.

To assess the endurance performance, the 6-min walk test [37] will be performed at pre- and post-assessment. The patients will be asked to walk a maximum distance in 6 min. The walking speed can be determined by the patient himself and changes and breaks will be allowed.

The applied total dose of antidepressant medication will be assessed by converting the fluoxetin equivalent doses (FED) and the medication on demand in mg/day according to the dose equivalents calculation of Hayasaka et al. [38].

The phases of the trial and the data collection at each timepoints are presented in Fig. 2.

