### Analysis

The trial will be analyzed by using the intention-to-treat principles, in which all patients with baseline data are included in the analysis. Adherence to intervention will be collected descriptive at each training session. The data are stored on the clinic’s own servers, which comply with a heightened security system. Missing data that are not directly related to adherence will be imputed, in order to include all participants. Differences between IG and CG from baseline to post-intervention will be determined by one-way repeated measure ANOVA for parametric and normally distributed data or the Friedman one-way repeated measure analysis of variance for non-parametric or non-normally distributed data. The level of significance is set at alpha ≤ 0.05. All computations will be performed using SPSS software (IBM Corporations, Armonk, NY, USA). No committee for data monitoring and auditing is planned.

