A serious issue in the hospital setting is the high level of physical inactivity among inpatients [43, 44]. A recent umbrella review indicates that higher physical activity levels in older adults have a 21% reduction in incident depression compared to older adults, who have lower levels of physical activity [45]. Physical inactivity leads to other risk factors such as sarcopenia [46, 47], loss of independence [48], and disability in ADL [49, 50]. Recent recommendations during hospitalization suggest that older inpatients should be as active as possible and incrementally enhance movement in everyday activities [51]. In addition, it is recommended that the influence of the physical environment should also be considered to enable older people to be active with portable adaptations and equipment for indoors and outdoors [51]. For this study, new types of ergometers will be placed on the wards to facilitate an environment that promotes exercise. From our point of view, this could counteract the loss of interest and decreased impulse known as key aspects in exacerbated periods of major depression. From our clinical experience, the variety of ergometers should increase the patients’ willingness for participation. It also offers advantages, for example when patients experience fatigue or pain in the lower limbs, they can still exercise while sitting on the ski ergometer. Therefore, this type of study is an important opportunity to strengthen physical activity in standard treatment.

This will be the first single-blinded RCT to examine physical interventions for the treatment of depression in an acute hospital setting. The outcomes of this trial can be directly transferred and implemented in the hospital. In order to include as many acute geriatric patients as possible, the inclusion criteria were chosen to include patients with mild cognitive impairment and bipolar disorder with depressive episodes.

Some limitations must also be considered; diverse factors in the TAU process could influence the success of decreased depression symptoms. The TAU, especially the pharmacological therapy, is expected to be effective in the treatment of depression symptoms. Another limitation is that the severity of depression symptoms, for example, a minimum score of the HAMD, is not an inclusion criterion. This study will be conducted in a geriatric psychiatry unit, where all of the included patients have a clinical diagnosis of depression, so symptom severity can be assumed.

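### Allocation is balanced on sex, age and MMSE, but the named tests include none of them, and the primary CGI rating is not adjusted for baseline severity

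*Protocol article*

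**What the plan says.** All places are in the protocol article.

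- **Allocation:** "With an informed consent and pre-assessment, randomization will be performed via stratified randomization". For balance between the groups, "the factors, sex, age, and MMSE score [29] will be weighted 1:1 in the program".
- **Primary outcome:** the CGI "includes a 1- to 7-point rating scale of the global improvement due entirely to treatment".
- **Secondary outcomes:** "the symptom domains and the severity of depressive symptoms will be measured by self- and peer-rated assessments". The instruments are the BDI II and the HAMD.
- **Analysis:** "Differences between IG and CG from baseline to post-intervention will be determined by one-way repeated measure ANOVA for parametric and normally distributed data". Where those conditions fail, the named alternative is the Friedman test. No covariate or stratification factor is attached to either test.
- **Sample size calculation:** a non-parametric analysis is expected because the instruments are ordinal. This points to Friedman for the CGI rating.
- **Discussion:** the authors list as a limitation that "the severity of depression symptoms, for example, a minimum score of the HAMD, is not an inclusion criterion".

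**The concern.** A trial that forces balance on chosen factors normally carries those factors into its analysis. Balanced allocation removes their contribution to the difference between arms. An analysis that ignores them still counts their variance as noise, so if they predict outcome the standard error is too large. The test then rejects too rarely under the null and loses power under the alternative.

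Baseline severity raises a second issue. It is not a randomisation factor and there is no minimum score for entry. The primary outcome is itself a rating of change, so a pre/post structure cannot bring severity into its analysis. Chance imbalance in severity is therefore handled neither by design nor by the primary analysis.

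Precision matters here because 50 patients per arm give much less power than the protocol states.

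**Working it through.** **1. The plan's own figure.** Inputs from the Sample size calculation: d = 0.5, two-sided alpha 0.05, power 0.95, 1:1, 100 patients.

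n per arm = 2 × [(1.960 + 1.645) / 0.5]² = 103.96, so 104 per arm and 208 in total (210 with the exact t test). The stated 100 is not reproduced from these inputs. With 50 per arm, the t test has noncentrality 0.5 × √(50/2) = 2.5 and power 0.697. At the SMD of 0.44 quoted in the same section, the noncentrality is 2.2 and power is 0.586.

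**2. Gain from adjustment.** Let r be the multiple correlation of the covariates with the outcome. The document gives no value, so r is assumed and the range starts at zero. Residual variance is multiplied by 1 − r², and the noncentrality becomes d × √(50/2) / √(1 − r²). Degrees of freedom are 98 unadjusted and 97 adjusted; using 94 changes no power by more than 0.001.

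| r | r² | power, d = 0.5 | power, d = 0.44 |
|---|---|---|---|
| 0 (unadjusted) | 0 | 0.697 | 0.586 |
| 0.1 | 0.01 | 0.701 | 0.591 |
| 0.2 | 0.04 | 0.714 | 0.604 |
| 0.3 | 0.09 | 0.737 | 0.627 |
| 0.4 | 0.16 | 0.771 | 0.662 |
| 0.5 | 0.25 | 0.815 | 0.711 |

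Example for r = 0.5: 2.5 / √0.75 = 2.887, power 0.815.

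**3. What 0.95 would need.** With 50 per arm at d = 0.5, solve 103.96 × (1 − r²) = 50. This gives r² = 0.52, or r of about 0.72.

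**4. Is the unadjusted test conservative?** Stratified allocation on three binary factors was simulated with N = 100 and near-equal allocation within strata. R² is the share of outcome variance that the factors explain.

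| R² | type I error, unadjusted | type I error, adjusted | power at d = 0.5, unadjusted | power at d = 0.5, adjusted |
|---|---|---|---|---|
| 0 | 4.9% | 4.8% | 69% | 69% |
| 0.10 | 4.0% | 4.9% | 71% | 74% |
| 0.20 | 2.8% | 5.2% | 71% | 78% |

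**5. Secondary HAMD and BDI II.** A pre/post analysis comparing two groups is equivalent to comparing change scores. With pre-post correlation ρ and unit SD, the change score has variance 2(1 − ρ) and ANCOVA leaves 1 − ρ². The ratio is (1 + ρ)/2, which is below 1 whenever ρ < 1. At an assumed ρ of 0.5 the variances are 1.00 and 0.75. Power at d = 0.5 with 50 per arm is then 70.5% and 82.3% (normal approximation).

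**The case against.** **Only an article is shown.** A covariate list is commonly left to an analysis plan, and nowhere does the text say the comparison is unadjusted. This has weight, and silence alone would not be a finding. But the Analysis section does not leave the method open. It names the tests, and the one that the Sample size calculation points to for ordinal instruments cannot hold the balancing factors. A later plan that added them would have to replace that test.

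**Repeated-measures ANOVA can be extended.** This is correct. A reader might infer that neither named test could carry covariates, but that is strictly true only of Friedman. For ANOVA the point is that no such extension is specified. Taken literally, the one-way label also leaves out the treatment arm. That is a separate and larger question, and a between-group model is needed in any case.

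**Baseline severity is used.** A reader might infer that the analysis ignores baseline severity altogether. The text does not support this: "Differences between IG and CG from baseline to post-intervention will be determined", so HAMD and BDI II baselines enter their own analyses as the first time point. Severity is absent only from the primary CGI comparison.

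**Severity may not vary much.** The missing HAMD threshold might suggest widely varying severity. No standard deviation or distribution is given, and the Discussion argues that severity can be assumed in this setting. Wide variation is therefore not established. Chance imbalance after randomisation is also not bias; the test's error rate covers it.

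**The gain is unknown, and the formula is for a normal outcome.** Both stand. Weak factors add almost nothing (0.701 to 0.714 at r = 0.1 to 0.2). In a proportional-odds model, covariates do not work by shrinking residual variance, so the table indicates scale only.

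**Conclusion.** The point holds as a mismatch between design and named analysis, with a loss of efficiency and no threat to validity. Sex, age and MMSE are balanced at allocation but absent from the tests as specified, the primary CGI rating has no adjustment for baseline severity, and HAMD and BDI II are analysed less efficiently than they could be.

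The error is on the conservative side. Its size depends on prognostic strength, which the document does not give: from nothing at r = 0 to about 12 percentage points of power at r = 0.5 (0.697 to 0.815 at d = 0.5). It would be tempting to read adjustment as a remedy for the sample size. It is not, because 0.95 with 100 patients needs r of about 0.72, which is not plausible for these covariates.

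The figures assume a normal outcome, 50 analysed per arm and no dropout. That baseline HAMD and BDI II precede randomisation is read from the Allocation section, which puts the pre-assessment first; the schedule figure is not available to confirm it.

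**What to change.** Prespecify, before any unblinded look at the data:

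1. **Primary outcome:** a between-group ordinal model for CGI improvement, for example proportional odds, with treatment, sex, age, MMSE and baseline HAMD. State that the target becomes a conditional odds ratio.
2. **Continuous secondary outcomes:** ANCOVA on the post-intervention value with treatment, that outcome's own baseline, sex, age and MMSE.
3. **Supportive:** the unadjusted between-group comparison for each.

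State whether age and MMSE enter as continuous variables or in the categories used at randomisation.

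The cost is a few sentences in the analysis plan. No new data or patients are needed: sex, age and MMSE come from the routine geriatric assessment, and HAMD and BDI II are already measured at baseline. Fixing the covariates now also rules out choosing them after the results are seen. The gap between the stated 0.95 power and 50 per arm has to be resolved separately.
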